## Abstract

**Background:**

Inflammatory response is one of the key components of pain perception. Continuous infusion (CWI) of local anesthetics has been shown to be effective in controlling pain and reducing postoperative morphine consumption, but the effect of adding a potent anti-inflammatory drug (such as a steroid) has never been addressed. In our study, we want to investigate the effect of CWI with local anesthetic + methylprednisolone on acute and persistent pain, correlating clinical data with biomarkers of inflammation and genetic background.

**Methods/Design:**

After approval by their institutional review board, three hospitals will enroll 120 patients undergoing major abdominal surgery in a randomized, double-blind, phase III study. After a 24-h CWI of ropivacaine 0.2 % + methylprednisolone 1 mg/kg, patients will be randomly assigned to receive either ropivacaine + steroid or placebo for the next 24 h. Then, patient-controlled CWI with only ropivacaine 0.2 % or placebo (according to the group of randomization) is planned after 48 h up to 7 days (bolus 10 ml, lock-out 1 h, maximum dose of 40 ml in 4 h). Morphine equivalent consumption up to 7 days will be analyzed, together with any catheter- or drug-related side effect. Persistent post-surgical pain (PPSP) incidence will also be investigated. Our primary endpoint is analgesic consumption in the first 7 days after surgery; we will evaluate, as secondary endpoints, any catheter- or drug-related side effect, genotype/phenotype correlations between some polymorphisms and postoperative outcome in terms of morphine consumption, development of the inflammatory response, and incidence of PPSP. Finally, we will collect, in a subgroup of patients, wound exudate samples by micro-dialysis, blood samples, and urine samples up to 72 h to investigate local and systemic inflammation and oxidative stress.

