Also, μ opioid receptor-1 (*OPRM1*) encodes the main receptor of opioids, and its polymorphisms are correlated to a significant interindividual difference in the postoperative consumption of morphine [21–23]. The catecholamine-O-methyltransferase (*COMT*) gene (encoding the enzyme that regulates the levels of catecholamines and enkephalins) has been associated with the variability of pain sensitivity in experimental, chronic, and postoperative pain [17, 20, 24]. The UDP-glucuronosyl-transferase 2B7 gene (*UGT2B7*) is of particular importance for the metabolism of morphine [25], but there are still very limited studies of the association between polymorphic gene expression, opioid treatment doses, and side effects.

Genetics could also be a predictor of the inflammatory response. The interleukin-1 receptor antagonist (IL-1Ra) is the main determinant of the bioactivity of IL-1, and the corresponding gene is polymorphic: variants of this gene have recently been demonstrated to be associated with differences in opioid consumption in the first 24 h after nephrectomy [26].

In our phase III study, we will investigate the analgesic effect of CWI with local anesthetic and methylprednisolone on acute pain and PPSP in the context of open abdominal surgery. Clinical data will be correlated with biomarkers of inflammation and to the genetic background in order to investigate (1) the role of both inflammatory mediators and oxidative stress in the genesis and maintenance of pain and (2) the contribution of gene polymorphisms on inter-individual differences in pain, response to analgesics, and inflammatory reaction after surgery.

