### Procedures - clinical study

On the day of surgery, patients come to the operating room and are provided with standard monitoring (electrocardiogram, oxygen saturation, non-invasive blood pressure, and invasive pressure monitoring). General anesthesia is given using propofol and midazolam (as deemed appropriate by the anesthesiologist), opioids (fentanyl 0.2 μg/kg or remifentanil 0.1-0.25 mg/kg per min or both), and muscle relaxants (cisatracurium/rocuronium) and maintained with sevoflurane.

A morphine bolus of 0.15 mg/kg is given 30 to 45 min before the end of surgery. An infusion catheter (Baxter Painfusor®; Baxter International, Deerfield, IL, USA) is placed by the surgeon in the fascial plane between peritoneum and fascia trasversalis, and a 10-ml bolus of 0.2 % ropivacaine is administered immediately after muscular plane closure; the catheter is then connected to an electronic pump (CADD®-Solis; Smiths Medical, Dublin, OH, USA) to give a continuous infusion of pain medications.

During the first 24 h, all patients receive ropivacaine 0.2 % + methylprednisolone 1 mg/kg, 10 ml/h (total volume of 240 ml in 24 h) continuous wound infusion; additionally, either acetaminophen 1000 mg or ketorolac 30 mg every 8 h is prescribed.

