### After 24 h, patients are randomly assigned between two groups of treatment:

Treatment group: 10 ml/h continuous infusion of ropivacaine 0.2 % + methylprednisolone 1 mg/kgPlacebo group: 10 ml/h continuous infusion of saline 0.9 %.

Regardless of treatment group, rescue analgesia in the first 48 h is provided by PCA pump with morphine (0.5 mg/ml, bolus 1 mg, lock-out 5 min, 20 mg limit every 4 h).

Random group allocation of patients is made through a computer-generated sequence. To maintain blinding, a research fellow who is not taking part in patient evaluation is in charge of preparing and programming all of the pumps used during the study: an opaque, sealed, sequentially numbered envelope is assigned to each patient and is opened by the same research fellow after the first 24 h of treatment.

Patients and their anesthesiologists are blind to treatment assignment. A clinical resident, who is not involved with randomization, is in charge of all clinical evaluations as part of the daily clinical practice.

The envelope is maintained apart from the patient’s case report form and is to be opened in every potentially harmful situation for the patient but only when care providers need to be aware of the patient’s treatment. All ropivacaine and methylprednisolone vials used during the study are registered with their code in order to be tracked and recognized in the future for any issue potentially hindering the validity of data.

At 48 h, morphine PCA is removed, and all patients are treated with Patient-Controlled Intrawound Analgesia (PCA through the wound catheter) with either ropivacaine 0.2 % alone or saline according to the group of randomization up to a maximum of 7 days after surgery. The catheter is removed at the seventh postoperative day or after 36 h of non-use (no self-administered bolus). After PCA removal, rescue additional analgesia is provided by tramadol (100 mg or 50 mg according to patient’s weight of not more than or of more than 50 kg).

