### Statistics

Sample size calculation was made on the hypothesis that the average morphine equivalent consumption in patients receiving local anesthetic and steroids CWI will be reduced by 50 % as compared with those in the control group. This assumption comes from (1) our retrospective experience and audits about analgesic consumption in our institution and (2) data from previous literature [27]; they both showed reduction in morphine consumption of 30–50 % in patients receiving local anesthetic wound infusion. Given this assumption, we need 50 patients per group for a power of 80 % and an α error of 5 %; given an attrition rate of 15–20 %, 120 patients are needed in each group.

We will perform an intention-to-treat analysis, and all participants will be analyzed once enrolled. We consider a “dropout” to be any patient not completing the evaluation at 3 months (for any reason).

For descriptive variables, we plan to use mean and standard deviation for normally distributed variables and average interquartile range for skewed distributions.

We will perform group comparison by using the Student’s *t* test or Mann–Whitney test for quantitative variables and Pearson’s chi-squared test for categorical variables. Inflammation, oxidative stress, and genetic background will be assessed to see whether they are biological markers that help modulate post-operative and persistent pain: the difference in inflammatory response and oxidative stress will be analyzed by means in a uni- and multi-variate regression model for repeated measures, including time, group, and their interaction. Variables will be transformed if needed to satisfy model assumptions. Post-hoc comparisons will include within-group changes over time and between-group differences at each assessment. The *P* value will be adjusted for multiple tests. Fisher exact test will be used to evaluate the impact of genetic background. The odds ratio and 95 % confidence interval will be computed with logistic regression. The *P* value to assess statistical significance will be corrected with the Bonferroni correction depending on the number of candidate genes tested.

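### The gene–morphine endpoint has no stated window and its named test cannot carry an arm term; adding pre-allocation 0–24 h PCA morphine and adjusting longer windows for arm would improve it at almost no cost

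*Protocol article*

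**What the plan says.** The abstract (Methods/Design) names the genetic objective as a secondary endpoint: "genotype/phenotype correlations between some polymorphisms and postoperative outcome in terms of morphine consumption". It gives no window, and Study outcomes adds none. The consumption endpoint that does have a window is the primary one, morphine equivalents over the first 7 days (abstract and Study outcomes).

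The Background justifies several genes by morphine or opioid response. UGT2B7 "is of particular importance for the metabolism of morphine"; OPRM1 is linked to differences in postoperative morphine use; IL-1Ra is linked to opioid use in the first 24 h after nephrectomy.

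Treatment changes twice within the 7 days:

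- 0–24 h: "During the first 24 h, all patients receive ropivacaine 0.2 % + methylprednisolone 1 mg/kg, 10 ml/h" (Procedures - clinical study).
- From 24 h: "After 24 h, patients are randomly assigned between two groups of treatment", active infusion or saline.
- Rescue to 48 h: "Regardless of treatment group, rescue analgesia in the first 48 h is provided by PCA pump with morphine".
- Rescue after 48 h: "After PCA removal, rescue additional analgesia is provided by tramadol", in one of two amounts set by body weight.

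Consumption is recorded at visits that include 24 h and 48 h. The Discussion uses 24-h morphine only to check for a difference between groups.

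On analysis, the Statistics section says "Fisher exact test will be used to evaluate the impact of genetic background", followed by logistic regression for odds ratios and a Bonferroni correction by number of candidate genes. In the same paragraph, the models for inflammation and oxidative stress include time, group and their interaction.

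**The concern.** A gene–morphine association is easiest to read when every patient titrates the same opioid under the same background treatment. Here that holds only before allocation. From 24 h, consumption also depends on the arm, and the plan expects the arm to halve morphine-equivalent consumption. From 48 h the rescue opioid is a different drug. If the genetic analysis used the one windowed measure in the text, it would combine two opioids and two randomised treatments in a single phenotype, and the first test named could not adjust for arm.

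At stake are the precision and the meaning of a secondary endpoint. The primary comparison is not affected.

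**Working it through.** **1. Sample available.** The abstract says "three hospitals will enroll 120 patients undergoing major abdominal surgery". From 50 per group, attrition of 15 % gives 50/0.85 = 58.8, so 59; attrition of 20 % gives 50/0.80 = 62.5, so 63. The total is therefore 118 to 126, and 120 in total corresponds to 1 − 50/60 = 16.7 % attrition. The Statistics section instead puts 120 in each group, which would mean 1 − 50/120 = 58 % attrition. That is a separate inconsistency; 120 in total is used here.

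**2. What the 7-day window contains, by time.**

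| Period | Hours | Share of 168 h | Wound infusion | Rescue opioid |
|---|---|---|---|---|
| 0–24 h | 24 | 14 % | same in all | morphine PCA |
| 24–48 h | 24 | 14 % | differs by arm | morphine PCA |
| 48–168 h | 120 | 71 % | differs by arm, patient-controlled | tramadol |

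Morphine PCA covers 48/168 = 29 % of the time. These are shares of time, not of consumption.

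**3. Arm effect implied by the sample size.** The inputs are 50 per group, 80 % power and 5 % alpha (two-sided assumed). No SD or control mean is given, so only the standardised effect can be recovered: d = (1.960 + 0.842) × √(2/50) = 0.560 by the normal approximation, or about 0.57 by the t test. For a 50 % reduction this means an SD of 0.5/0.56 = 0.89 of the control mean.

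**4. Cost of leaving arm out.** With 1:1 allocation, pooling the arms adds d²/4 to the within-arm variance.

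- Variance: 1 + 0.560²/4 = 1.078.
- Standardised gene effect: 1/√1.078 = 0.963 (0.962 with d = 0.566), a loss of about 4 %.
- Effective sample: 120/1.078 = 111 of 120.
- Power: five candidate genes are listed, so alpha is 0.05/5 = 0.01. For a gene effect with 80 % power when arm is accounted for, (2.576 + 0.842)/√1.078 − 2.576 = 0.715, which gives 76 %.

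Analysing each arm separately would cost far more: 3.417/√2 − 2.576 = −0.16, or 44 % power. An arm term keeps all patients and removes the pooling loss if there is no gene-by-arm interaction.

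**5. Margin available.** For a carrier versus non-carrier difference in means at alpha 0.01 and 80 % power, the detectable difference is 3.417 × √(1/(120f) + 1/(120(1 − f))). This gives 0.78, 0.68 and 0.62 SD for carrier frequencies f of 0.2, 0.3 and 0.5. The frequencies are assumptions, as the document gives none.

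**Limits.** Steps 4 and 5 treat consumption as a mean. Fisher's test and logistic regression need a categorised outcome, so the figures are indicative. The d in step 3 belongs to the 7-day endpoint. The arm effect on 0–48 h morphine is not given and may differ, because the arms share the first half of that window.

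**The case against.** The strongest reply is that the document never ties the genetic objective to the 7-day total. It says morphine consumption, while the trial outcome is called morphine equivalents. Read literally, the genetic phenotype could be PCA morphine over 0–48 h, which contains no tramadol. Windows and covariates for a secondary candidate-gene analysis are also commonly left to a full protocol or SAP, and neither is shown. This stands against any claim that the plan has chosen a mixed-opioid phenotype. It does not remove the arm point: a 0–48 h window still crosses allocation at 24 h, and Fisher's exact test is a method the article states.

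A reader might infer that chance genotype imbalance between arms would appear as a gene effect. Allocation is random and so independent of genotype; chance imbalance is ordinary sampling error within the test's alpha.

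A reader might also want to put a number on the tramadol dilution. That needs the spread of tramadol use relative to morphine, and the assumption that it is unrelated to the genes. The document supports neither. The Background describes OPRM1 as encoding the main opioid receptor and links COMT to pain sensitivity, so later rescue use may carry gene signal as well as noise. The Discussion adds that pain is traditionally considered highest in the first 48 h, so time shares do not give consumption shares.

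Finally, 0–24 h is not a clean window. Patients have had a weight-based intraoperative morphine bolus, receive either acetaminophen or ketorolac, and are all under ropivacaine and methylprednisolone. Later days also matter to a trial concerned with sensitisation and persistent pain. This is why the early window should be added without displacing the longer ones.

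**Conclusion.** The point holds as a modest, well-defined improvement. The gene–morphine endpoint has no stated window, the one windowed consumption measure mixes two opioids, and any window beyond 24 h spans the randomised split. The stated genetic test cannot adjust for that split, and no arm term is named for the regression.

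The unadjusted analysis is valid but slightly imprecise. It loses about 4 % of the standardised effect, equivalent to about 111 of 120 patients, or power falling from 80 % to about 76 %. This rests on the arm effect implied by the sample size (d about 0.57), two-sided alpha, 1:1 allocation and a comparison of means. The effect of including tramadol cannot be sized from the document. The stronger conclusions, that the association would be uninterpretable or that arm would create false gene effects, are not supported.

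**What to change.** In Study outcomes and Statistics:

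1. Add cumulative PCA morphine over 0–24 h, pooled over all patients before allocation, as a pre-specified phenotype for the opioid-response genes.
2. For any longer window (0–48 h PCA morphine, 7-day morphine equivalents), include randomised arm as a covariate in the regression, and state which window each genetic analysis uses.

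The cost is wording only. Consumption is already recorded at 24 h and 48 h, and genotyping is planned in all patients. The downside is small: the 0–24 h phenotype says nothing about later days, and it reflects morphine need under the common infusion, after the intraoperative bolus and with either co-analgesic. It should be described as free of arm and tramadol effects, not of these.

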**Discussion:**

This is a phase III trial to evaluate the safety and efficacy of wound infusion with steroid and local anesthetic. The study is aimed also to evaluate how long this infusion has to be maintained in order to maximize effectiveness. Our data are intended to quantify the amount of ropivacaine and methylprednisolone needed by patients undergoing major abdominal surgery, to be stored in a new nanotechnology device for sustained pain treatment after surgery. We also aim to clarify the roles of inflammatory response, oxidative stress, and genetic background on postoperative and persistent pain after major abdominal surgery.

**Trial registration:**

The trial was registered on ClinicalTrials.gov (NCT02002663) on 24 Oct. 2013.

## Background

Acute postoperative pain is a complex unresolved phenomenon sustained by various patho-physiological changes, potentially leading to postoperative morbidity and persistent post-surgical pain (PPSP) [1], influencing patient outcome [2–4]. Risk factors for PPSP have not been completely established yet, but the severity of acute postoperative pain is often mentioned [5]. Therefore, postoperative pain relief is gaining further interest in the perspective of an improved long-term outcome after hospital discharge.

Postoperative pain treatment involves different strategies; the paradigm of multimodal analgesia is to combine different techniques and drugs to improve efficacy and reduce side effects. The most challenging target is the reduction of opioid consumption because, beyond the well-known respiratory, cognitive, and digestive side effects, opioids may be associated with immune depression and distant malignant cell proliferation and expansion after oncologic surgery [6, 7].

In this perspective, continuous wound infusion (CWI) has gained increasing interest in the last decade. CWI prolongs the action of local anesthetics, improving their efficacy, and has been shown to be effective in controlling pain and in reducing postoperative morphine consumption in major surgery [8]. A further advantage of CWI is the ability to provide a continuous block of pain stimuli coming from the periphery, thus continuously providing protection from central sensitization and pain persistence: the incisional pain model has clearly demonstrated that single-administration, pre-incision analgesia (i.e., preemptive analgesia in clinical practice) is of little interest because when the effects of analgesic treatment abate, the wound itself is able to restart sensitization processes. Therefore, the question is how long continuous infusion should be maintained after surgery.

Nevertheless, postoperative pain is due to different components, and the inflammatory reaction and its non-resolution are now considered to be important factors underlying both acute pain and pain persistence after surgery [1, 9, 10]. A reasonable approach to reduce the inflammatory response is to modulate its local expression with anti-inflammatory agents. Despite the studies that have investigated the efficacy of wound infusion with non-steroidal anti-inflammatory drugs and despite proofs of clinical analgesic efficacy [11], it is well known that cyclooxygenase (COX)-induced enzymes account only partially for local inflammation and that several other substances—especially cytokines and interleukins (ILs)—are involved in the process [12] together with oxidative stress [13]. Although the relative importance of each cytokine may differ depending on the type of surgery, the pro-inflammatory IL-1-β seems to play a major role in incisional pain: it is required for the induction and maintenance of incisional pain in animal models and may contribute to the variation of postoperative morphine consumption in humans [14]. Thereby, the modulation of local cytokine production might represent an attractive alternative for the future developments of intrawound analgesia [15], and the administration of a steroid could be more promising than non-steroidal anti-inflammatory drug infusion [16].

Despite the importance of analgesia, the genetic contribution is considered a determinant for PPSP development, and different studies have highlighted the role of genetic factors on postoperative outcome in terms of analgesic response and pain intensity [17, 18].

Literature data demonstrate that the gene codifying for the adrenergic receptor α-2 (*ADRB2*), a target for adrenaline, is characterized by some single-nucleotide polymorphisms (SNPs) predisposing patients to chronic pain [19]. Diatchenko et al., genotyping 202 females, found that particular *ADRB2* haplotypes modulate chronic pain conditions such as temporomandibular disorder [20].

Also, μ opioid receptor-1 (*OPRM1*) encodes the main receptor of opioids, and its polymorphisms are correlated to a significant interindividual difference in the postoperative consumption of morphine [21–23]. The catecholamine-O-methyltransferase (*COMT*) gene (encoding the enzyme that regulates the levels of catecholamines and enkephalins) has been associated with the variability of pain sensitivity in experimental, chronic, and postoperative pain [17, 20, 24]. The UDP-glucuronosyl-transferase 2B7 gene (*UGT2B7*) is of particular importance for the metabolism of morphine [25], but there are still very limited studies of the association between polymorphic gene expression, opioid treatment doses, and side effects.

Genetics could also be a predictor of the inflammatory response. The interleukin-1 receptor antagonist (IL-1Ra) is the main determinant of the bioactivity of IL-1, and the corresponding gene is polymorphic: variants of this gene have recently been demonstrated to be associated with differences in opioid consumption in the first 24 h after nephrectomy [26].

In our phase III study, we will investigate the analgesic effect of CWI with local anesthetic and methylprednisolone on acute pain and PPSP in the context of open abdominal surgery. Clinical data will be correlated with biomarkers of inflammation and to the genetic background in order to investigate (1) the role of both inflammatory mediators and oxidative stress in the genesis and maintenance of pain and (2) the contribution of gene polymorphisms on inter-individual differences in pain, response to analgesics, and inflammatory reaction after surgery.

